#### **4. Study procedures:**

##### *1) General study design.*

This is a two-arm randomized control trial design. Twenty local counselors and 4 clinical supervisors working with three local organizations in Mae Sot have been trained by JHU or other US-based clinical psychologists to provide the CBI intervention to all the survivors they treat. CBI is a 'components-based' intervention that includes psychoeducation, relaxation, life-enhancing skills (problems solving and safety planning), family support, and cognitive processing of life problems and traumatic events, in a specific way, and is based on the current standard of practice for trauma-affected clients. Approximately half of those found eligible for the trial will be randomly allocated to the case group to receive the intervention immediately and the other half will be asked to wait for approximately 3 to 4 months before being reassessed and then receiving the intervention being provided by the counselors. The wait-control group will form the second arm of the trial.

##### *2) Study procedures, including their sequence and timing.*

*Recruitment:* Beginning in May 2011, recruitment for the intervention effectiveness study will begin. Recruitment of persons for screening and enrollment will be done by contacting the local organizations and inviting program beneficiaries and community members to come to the counselors to be screened. Recruitment will be done by word-of-mouth and through routine program contacts with the community. Local partner organizations (BBP, AAPP, MTC and SAW) have developed a one-page handout and pamphlet in the local language (Burmese) that provides a brief description of the project and contact information for persons in the project whom they can contact for more information. These contact persons with the local partner

organizations will then collect names and contact information for those who express interest in possibly taking part in the study. The recruitment process will identify the availability of a new intervention for people who have experienced or witnessed torture or systematic violence and who feel they might benefit from counseling for depression or trauma symptoms. Potential participants will be told that the program is available for Burmese persons 18 years or older who will remain in the Mae Sot area for the duration of the intervention (10 weekly sessions). Persons expressing an interest in being contacted for a follow-up discussion will be invited to provide their contact information to the local program staff-members as mentioned above. We anticipate that the recruitment process will take approximately 4-8 weeks, to be carried out as counselors and clinical supervisors are completing a practicum period of training in the CBI method (March – June 2011). All contact information will be collected from the local partner organizations by the on-site JHU Project Director who will maintain the overall file of potential clients for the study. Local partner organizations will be asked to destroy their copies of the names and contact information as this will be maintained only by the Project Director on a secure file.

*Training on Consent and Screening Procedures:* We plan to begin the actual intervention study with CBI in June 2011 (corresponding to Month 5 in the table below). Prior to that, JHU study faculty will provide training to all counselors and clinical supervisors on how to carry out consent and screening procedures, including administering the study consent form and interpreting depression and trauma severity scores.

*Screening:* A screening process, and allocation to either an intervention (case) group or temporarily to a wait-control group, will continue until the practicum round of CBI training has been completed in late June or early July. If a sufficient number of clients for the intervention group are not identified by early July, screening and enrollment could continue beyond that time.

*Service Provision:* Beginning in late June or early July 2011, the intervention will begin with weekly sessions provided by the counselors to the client and with supervision provided in the form of weekly meetings between the counselor and clinical supervisor and in the form of weekly phone conversations between the clinical supervisors and the JHU trainers/clinical psychologists. Both intervention and control clients will be monitored using separate client monitoring forms. These forms will include information on the clients' well-being, any treatment or medication they are receiving, and whether or not the client's are in danger to themselves or others. Clients who are in danger of committing suicide will be discussed immediately with supervisors, or referred if supervisors are not immediately available. There is a Safety Plan (see attachment) in place for this project that includes a response team of the following: the counselor, the counselor's clinical supervisor, a medical doctor who is part of the project team, and the Field Project Coordinator. The Project Director will provide support for this response team at all times and will be in regular contact with the Project PI. A copy of the Safety Plan protocol is included in the IRB application.

Persons who are in the intervention group or the wait control group whose depressive symptoms worsen (but not to the point of ineligibility) would first be evaluated by the counselor in conjunction with the study's clinical team and with the CCT medical monitor. Based on this assessment, a decision could be made to continue CBI treatment alone or the client could be provided referral to standard of care treatment possibly including non-specific counseling. This treatment would be recorded in the client monitoring records.

We should note that some of the counselors who will deliver the CBI intervention are also qualified to provide other services (for example, some of the Mae Tao Clinic counselors providing the intervention also work at the Counseling Center on a part-time basis). We will ask for the period of the intervention, that the CBI counselors provide only CBI to their study clients. If referrals are made for other services (or clients independently seek other services including,

possibly, non specific counseling) these other services would be provided by someone other than the CBI counselor.

|                                                               | Month |    |    |    |    |    |    |    |    |    |    |    |
|---------------------------------------------------------------|-------|----|----|----|----|----|----|----|----|----|----|----|
|                                                               | 1     | 2  | 3  | 4  | 5  | 6  | 7  | 8  | 9  | 10 | 11 | 12 |
| 1. Training on CBI Method                                     | XX    | XX |    |    |    |    |    |    |    |    |    |    |
| 2. Practicum Round on CBI                                     |       |    | XX | XX | XX |    |    |    |    |    |    |    |
| 3. Recruitment                                                |       |    |    | XX | XX |    |    |    |    |    |    |    |
| 4. Screening and Baseline Interviews of Case and Wait-Control |       |    |    |    | XX | XX |    |    |    |    |    |    |
| 5. Intervention (Case Group)                                  |       |    |    |    |    | XX | XX | XX | XX | XX |    |    |
| 6. Follow-up Interviews (Case and Wait-Control Groups)        |       |    |    |    |    |    |    |    |    | XX |    |    |
| 7. Intervention for Wait-Control Group                        |       |    |    |    |    |    |    |    |    | XX | XX | XX |
| 8. Study Wrap-up                                              |       |    |    |    |    |    |    |    |    |    | XX | XX |

*Follow-up interviews.* All follow-up interviews (including with the wait-control group) will be conducted at the end of the intervention for the case group, which would be no more than 3 to 4 months after the date of enrollment into the study.

Following completion of the trial, the data will be analyzed, and if the intervention is found to be effective, it will become part of the services provided by the counselors to torture and violence survivors.

### 3) *Number of study contacts or visits required of participants*

We expect at most 2 research contacts with each intervention participant for the purposes of the study - the initial screening and the post-intervention interview. Wait-control group individuals will also receive monthly contacts during their waiting time, totaling 3 to 4 contacts during the trial.

### 4) *Expected duration of the study*

We expect the study will last approximately 12 months, including the data analysis period. The two phases of the intervention—CBI for the case group and CBI for the wait-control group (if it is established as effective)—we expect to be concluded by the end of December 2011.

### 5) *A brief data analysis plan and description of the nature of the variables to be derived*

As noted previously, depression and trauma were the two mental health problems that were prominently identified in the qualitative research (IRB#3047) that preceded this intervention evaluation phase of the project. Depression symptoms will be measured using a modified, locally validated version of the Hopkins Symptoms Checklist (HSCL) and trauma exposure and symptoms will be measured using a modified, locally validated version of the Harvard Trauma Questionnaire (HTQ). The data generated from the validation study has been used to develop depression and trauma scale cutoff scores for the study population. The counselors will calculate the total score for these subscales during the initial screening interview, since scores on either of these scales above the cutoffs are part of the eligibility criteria (13 or above for

depression symptoms and 45 or above for trauma symptoms). Following randomization into a case group and a wait-control group, the counselors will provide the intervention to the case group. At the end of the intervention, the case group and the wait-control group will be re-interviewed using the same instrument employed in the screening interview. The mean change in the various subscales between pre and post intervention interviews will be calculated and subtracted from the mean change (calculated in the same way) for the wait-control group. The differences will be the amount of change on each scale due to the intervention.

In terms of statistical analysis, we will keep the data on study participants in the intervention group who get other standard of care treatment or participants in the wait-control group who need immediate treatment. All study participants who meet screening criteria for eligibility and enroll in the study will be included in the analysis on an intent to treat basis.

6) *If human biospecimens (blood, urine, saliva, etc.) will be collected, provide details about collection, volume (ml) or number, use, storage, identification, and disposal.*

Not Applicable

7) *Describe how subjects will be screened for eligibility and assigned to study/intervention and comparison/control groups.*

All adults who meet with one of the 20 trained counselors will be verbally consented and screened by the counselors for study eligibility. Counselors will first re-confirm that the person lives in Mae Sot, will be available for the duration of the study, and is 18 years or older. The screening interview will then be used to establish whether the individual meets our definition of exposure to torture or systematic violence (experienced or witnessed at least one trauma exposure event), and has significant depression and/or trauma symptoms (as noted previously, the scores are 13 or above for depression symptoms and 45 or above for trauma symptoms).

Exposure to torture and violence will be measured through a review of the trauma exposure questions on the assessment interview. There are 25 questions that ask about exposure to traumatic events. If the respondent indicates that they personally experienced or witnessed any of these for exposures, they will be regarded as having been exposed to torture for purposes of this study. If they are not eligible for our study, they can continue to receive counseling and support as per existing standards of care and service provided by the local participating organizations.

Measures of trauma or depression symptoms will be based on the responses to all trauma and depression questions in the screening interview. The counselors will calculate the total score for these questions (defined as the total trauma and depression subscales) while the interviewee is still present. If this meets or exceeds a cutoff score of 45 for trauma---reflecting likely clinically significant symptoms (based on results of a previous validity study of the instrument among the same population) and/or a cutoff score for depression of 13 or more ---reflecting likely clinical significant depression (again based on results of the previous validity study)---then the person will be invited to join the trial after having been read a consent form which explains the trial. If they agree they will be assigned either to receive treatment beginning soon or be told that they are on a wait-list and will need to wait several months before receiving treatment. If they are eligible but decline to participate in the trial, the counselor and clinical supervisor, in consultation with the JHU study team, will review treatment options on a case-by-case basis. Depending on the outcome of this assessment, these individuals could be offered to receive the study treatment (though not participate in the study) or they could be referred to other appropriate programs and services in the Mae Sot area.

While the study imposes no upper cut-off point for depression and trauma symptoms (and thus would not exclude persons with acute mental illness), there may be some individuals who are deemed eligible and have consented to participate in the study but who would be excludable either because they are a danger to themselves or others, or who are psychotic or otherwise deemed not competent to give consent or participate in the interventions. While we believe the study intervention is not appropriate for these individuals, counselors will review the cases with their clinical supervisors and the JHU study team to ensure that every effort is made to provide these individuals with referral to appropriate care.

In the case of individuals who evidence signs of active suicidal ideation, counselors and clinical supervisors have been trained on suicide assessment as part of their CBI training. In all cases involving potential danger of a client harming him/herself or others, counselors will follow the study Safety Plan to request assistance in assessing the need of follow-up care and services for that individual. On a case-by-case basis, the study team will work with the counselor and clinical supervisor, along with [name] and the study team's clinical experts, to determine whether to offer the individual the study treatment (if they are excludable from the study intervention), or the study intervention (if they are otherwise eligible and no longer deemed an active risk to harm themselves or others), or some other available and appropriate treatment.

*Randomization process:*

If the subject is deemed eligible and consents to join the trial, the subject will be randomly allocated to the case group to receive treatment immediately or to the wait-control group. The randomization process will be as follows:

1. Each counselor will receive a list of participant ID numbers in sequence (i.e. 1-15) which have been randomly allocated to either intervention or wait-control via a random number generator, with a 1 to 1 ratio of intervention to wait-list. There will be one list for each counselor. Counselors will not be aware how numbers have been allocated.
2. For each counselor, a paper indicating the treatment assignment (intervention or wait-list) will be folded and stapled directly to the back of consent forms that are pre-numbered with a client ID number.
3. Once the subject has consented to be in the study, the counselor will assign a number to the client in the order in which they are recruited. They will remove and unfold the paper attached to the form that corresponds to their ID number, and will inform the subject whether they will begin the intervention immediately or will be put on the wait list.

The study investigators will keep master lists for each counselor which indicate the allocated group status (intervention or wait-control) for each client ID number to ensure fidelity to the randomization model.

Persons in the wait-control group will be instructed to contact their counselor, either by phone or in person, if their symptoms worsen during the wait period. The Field Program Coordinator will work with the counselors to coordinate a process of check-in (either in person or by phone) with wait-control clients every month for assessment of symptom severity by the counselors. In cases where the symptoms are worse, this will be reported to the clinical supervisors and the JHU study team and a decision made about whether the participant should be referred for additional services. In severe cases where the person is a risk to themselves or others the project will follow the Safety Plan (explained above).

*8) Explain and justify whether there will be blinding.*

In this study, the follow-up interviews of the case group clients will be carried out by counselors different from those who provided the CBI treatment. Follow-up interviews will be randomly assigned to counselors who will be blind to the initial assessment scores of the interviewee and who would not have knowledge of a client's results during the CBI intervention. This will eliminate risk of bias on the part of counselors who might wish to improve the outcome scores of their client caseload and would promote rater independence between the pre- and post-intervention measures.

*9) Explain and justify whether participants will not receive routine care or will have current therapy stopped*

Standard care for Burmese displaced persons with mental health problems in Mae Sot could include treatment at Mae Tao Clinic's Counseling Center where treatment includes non-specific counseling and (frequently) medication. Cases involving active suicidal ideation or psychotic breakdown could be provided in-patient treatment at Mae Tao Clinic or referral to Mae Sot Hospital where psychiatric services are provided. Mae Sot Hospital is a facility primarily for the local Thai population and is not routinely used by the Burmese population for reasons of cost, insecurity (due to travel risks and possible contact with Thai authorities) and language incompatibilities. In the case of psychiatric services, this usage of Mae Sot Hospital by the Burmese migrant community has been limited generally to emergency cases involving, for example, a suicide attempt (or active suicidal ideation) or a severe psychotic episode. Mae Tao Clinic, on the other hand, is a site that Burmese migrants may be more likely to use for mental health services. MTC's Counseling Center provides on-site, non-specific counseling services and MTC also provides some inpatient care. Both the Counseling Center and the inpatient services tend to include some medication as part of treatment. Participation in the CBI intervention does not require that an individual discontinue other treatments or therapies nor would they be discouraged from using other services during the course of the study intervention. The study seeks to compare the effect of the CBI intervention against no CBI intervention. We are not comparing the CBI intervention with other available treatments. Thus, for individuals in the intervention group who may experience a worsening of symptoms or individuals in the wait-control group who need immediate services a decision to refer to standard of care treatment would be made on a case-by-case base following discussions by the treatment team—the counselor, clinical supervisor, and the clinical team ([name] and the JHU clinical experts). Use of any such services, including medications (if any) would be discussed in the CBI counseling sessions and documented in the client monitoring records.

*10) Explain and justify the use of a placebo or non-treatment group.*

No placebos will be used. There will be a wait-control group who will not initially receive treatment. Instead they will wait until the intervention has been completed for the case group, a period of no more than 3 to 4 months. They will then be reassessed before beginning treatment. The reason for the initial non-treatment is that we do not have evidence of the effectiveness in this setting for the treatment included in the study.

Once wait-control group participants have waited the full intervention period (3 to 4 months), they will then receive the intervention from the counselor they saw at intake (unless it is established that the intervention is shown to be unhelpful or harmful). In addition, controls will be provided the study therapy if their symptoms become clinically significantly worse, or (in severe cases where the person is a risk to themselves or others) they may be referred to other sources of care (either Mae Tao Clinic or Mae Sot Hospital).

*11) Provide a definition of treatment failure or participant removal criteria.*

Clinical treatment failure is defined as an individual completing less than 6 sessions of the Components-Based Intervention. Available research suggests that this is a significant “dose” of therapy to see treatment effects. The success or failure of the intervention failure will not be assessed at the individual level but only at the group level. Failure at the group level for the intervention would consist of less than a 20% difference in change in mean symptom severity score between pre and post intervention assessment compared with the wait-control group.

Participants would be assessed on a case-by-case basis if they were in danger of suicide or doing harm to others. This will be defined by demonstrating actively suicidal or homicidal thoughts. At that point, the counselors will work with their supervisors to seek more specific psychiatric assistance with the individual.

*12) Describe what happens to participants receiving therapy when the study ends or if a subject's participation ends prematurely.*

At the end of the study those counselors providing interventions found to be effective will continue to provide treatment, both to those currently receiving the treatment and to new clients. Persons who have not yet received the new intervention will be eligible to receive it regardless of whether they had previously received any treatments. If a subject's participation ends prematurely for whatever reason, they could continue to work with a clinician or other care services as needed.

Any participant who does not come to a regularly scheduled session will be followed up by the counselor to determine whether they are a formal withdrawal or if there is some other barrier that can be overcome to continue treatment. If the participant does not want to participate further, the counselor or project staff will try to find out the reason for withdrawal. Otherwise, no further action will be taken. Our sample size calculations are based on an assumption that about 25% of participants will choose to withdraw from the study and from treatment.

*13) Describe the process for referring subjects to care outside the study, if needed.*

One local counterpart, Mae Tao Clinic, operates a primary care clinic with a Counseling Center and with referrals to Mae Sot Hospital, a Thai hospital in Mae Sot with limited in-patient psychiatric services. Clinical supervisors for the CBI intervention will be in weekly contact with JHU and consulting CBI experts on a routine basis and will communicate with them on an as needed basis. Persons who are found at screening or during the study to be in active danger of harming themselves or others will be immediately discussed with clinical supervisors and the safety response team for referral to the nearest and most appropriate treatment site.

*14) For studies that evaluate interventions, have a randomized study design, and/or are a clinical trial, provide power calculations for projected sample size.*

To calculate sample size, we relied on a pair-wise comparison – that is comparing the intervention to the wait-control condition. We calculated sample size and power calculations using effect size analyses of depression and trauma symptom scores. We estimated that to find a moderate effect size (.50) for either depression or trauma, we would need 120 participants in each arm. We used power=0.80, alpha=0.05, a design effect of 1.5, a drop-out rate of 25%, and a 1:1 ratio of intervention (case) to wait-control.

Based on our experience of both client and counselor drop-out and other challenges (i.e. people moving), we chose to inflate the recruitment sample size needed for each arm to 150, resulting in 300 participants. Given the rates of depression and trauma symptomatology found during the previous validity study, we estimate needing to screen approximately 400 torture survivors to identify 300 eligible and willing participants.

15) Describe any plan for reporting test results to participants.

After the intake interview is complete, the counselors will review the results of the depression symptoms subscale (Questions 3.1 – 3.17 in the screening/assessment instrument) and the trauma symptoms subscale (Questions 4.1 – 4.30) and will share these with the client. Data from the other scales will not be available to the clients at the time of the intake screening.

At the completion of the study, all study participants, including wait-controls at that time, will be told what the general results were and informed as to their options for receiving continuing or alternative forms of treatment.

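### The described contrast pools the arms, although participants are randomised within counselor and the sample size includes a design effect of 1.5

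*Protocol*

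**What the plan says.** Three parts of Section 4 of the protocol bear on this point.

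- **Allocation (item 7, randomization process).** An eligible, consenting person is allocated individually: "the subject will be randomly allocated to the case group to receive treatment immediately or to the wait-control group". The allocations come from pre-generated 1:1 lists, and "There will be one list for each counselor". There are 20 counselors, and the example list runs to 15 IDs, which matches the target of 300. Every counselor's list therefore contains both arms.
- **Sample size (item 14).** The plan states that "to find a moderate effect size (.50) for either depression or trauma, we would need 120 participants in each arm", and gives the inputs: "We used power=0.80, alpha=0.05, a design effect of 1.5, a drop-out rate of 25%, and a 1:1 ratio of intervention (case) to wait-control". It does not say which unit the design effect refers to, or what ICC and cluster size lie behind it. Recruitment is then raised to 150 per arm.
- **Analysis (item 5).** The effect on each scale is the case arm's mean pre-post change minus the wait-control arm's, by intention to treat. The text then says: "The differences will be the amount of change on each scale due to the intervention". It names no counselor term, test, standard error, confidence interval or model.

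Items 5, 8 and 10 add who does what. Counselors treat the case group. Wait-controls get monthly check-ins and are due to receive CBI later from their intake counselor. Case clients are re-interviewed by a counselor other than the one who treated them.

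**The concern.** The sample size treats outcomes as correlated and pays for that with 50% more participants. The randomisation makes counselor a stratum. The contrast in the analysis plan uses neither fact, so the three parts of one document rest on different assumptions.

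What is at stake is the precision attached to the result. Counselors can affect outcomes in two ways, and these push in opposite directions:

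- If a counselor's clients do better or worse in both arms alike, that difference cancels within each list. A test that ignores counselor then uses too large a standard error.
- If counselors differ in how well they deliver CBI, the variation falls mainly on the case arm, because only that arm is scheduled to receive therapy during the comparison period. It does not cancel, and a test that ignores it uses too small a standard error.

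**Working it through.** **1. Is the design effect really in the 120?**
Inputs from item 14: d = 0.50, power 0.80, alpha 0.05 (two-sided assumed), design effect 1.5, dropout 25%.
- A two-sample t-test needs 64 per arm.
- 64 × 1.5 = 96, and 96 × 1.25 = 120. This reproduces the plan's figure.
- Without the design effect, the result is 79 to 86 per arm, depending on the base n (63 or 64) and on whether dropout multiplies by 1.25 or divides by 0.75.

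So the 1.5 is a working part of the calculation. (Dividing by 0.75 with the design effect kept gives 128, which the 150 per arm covers.)

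**2. What ICC would 1.5 imply?**
From 1.5 = 1 + (m − 1) × ICC, ICC = 0.5/(m − 1).
- m = 15 (a whole list): 0.5/14 = 0.036.
- m = 7.5 (one arm of a list): 0.5/6.5 = 0.077.

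The protocol does not say which is meant. Below, the ICC is an assumption, shown over 0.01 to 0.10.

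**3. Counselor effect shared by both arms.**
Ratio of the pooled to the true standard error = 1/√(1 − ICC). Type I error = 2 × [1 − Φ(1.96 × ratio)].
- ICC 0.01: ratio 1.005, type I error 4.9%.
- ICC 0.10: ratio 1.054, type I error 3.9%.

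**4. Counselor effect in the treated arm only.**
With m treated clients per counselor, ratio = √(2/(2 + (m − 1) × ICC)), and type I error follows as in step 3.
- m = 7.5, ICC 0.01: ratio 0.984, type I error 5.4%.
- m = 7.5, ICC 0.077: ratio 0.894, type I error 8.0%.
- m = 7.5, ICC 0.10: ratio 0.869, type I error 8.9%.
- m = 5.625 (7.5 × 0.75, completers only): 5.3% at ICC 0.01 and 7.7% at ICC 0.10.

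**5. Simulation check.**
Setting: 20 counselors with 15 clients each, 75% evaluable, nominal 5%, 3,000 to 4,000 null runs per setting. The variances are assumed.
- No counselor effects: the pooled t-test rejects in 5.0% of runs.
- CBI effect varying between counselors with variance 0.05, ICC 0 to 0.05: 6.1%.
- The same with variance 0.10 (SD 0.32 outcome SDs): 7.3-7.9%.
- A one-sample t-test on the counselors' within-list differences stays at 4.6-5.4% throughout.
- At d = 0.5 with no counselor differences, that test has about 92-93% power, against 96% for the pooled test.

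**6. Baseline adjustment.**
With equal variances and pre-post correlation ρ, a change-score contrast has variance proportional to 2(1 − ρ), and a baseline-adjusted one to 1 − ρ². Their ratio is (1 + ρ)/2, which is below 1 whenever ρ is below 1. For an assumed ρ of 0.3 to 0.7 it is 0.65 to 0.85.

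**The case against.** The strongest reply is that nothing stated is wrong. The section calls itself brief and defines only a point estimate. With individual 1:1 allocation inside each list, that estimate is unbiased whether or not counselor is modelled. The test and standard error may stand in an analysis plan that is not shown. All of this stands, so a reader should not infer that stated p-values or intervals are invalid: the protocol states none. The sentence quoted from item 5 concerns the estimate and says nothing about its variance.

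It can also be said that the design effect is not wasted, since it protects power under any model. This stands too. With 150 recruited per arm and 25% loss, 112.5 remain, and power at d = 0.50 is 0.86 with the design effect and 0.96 without it.

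The sizes rest on assumed values, and the two mechanisms can offset each other. Further, variation in the CBI effect between counselors inflates the error only if these 20 are taken to represent a wider population of counselors. If inference is about these 20 alone, it does not. That is a choice of estimand, and it is why the random arm effect belongs in a sensitivity analysis and not in the primary model.

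Two stronger readings are tempting and fail:

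- The separate lists might suggest cluster randomisation. Item 7 allocates individuals, and each counselor has both arms.
- A reader might apply the whole 1.5 to the contrast and obtain a type I error of 2 × [1 − Φ(1.96/√1.5)] = 11%. Because both arms sit within each counselor, the 1.5 does not carry over in full. With clustering in the treated arm only, ICC 0.077 and m = 7.5, the contrast's design effect is 1 + 6.5 × 0.077/2 = 1.25, and type I error is about 8%. Reaching 1.5 would need an ICC of 1/6.5 = 0.15.

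What remains is that the one contrast the protocol does describe leaves out the strata used for allocation and the clustering assumed in the sample size, and that the 1.5 is unexplained.

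**Conclusion.** The point holds as an improvement at almost no cost, not as a demonstrated error. The described contrast is unbiased but does not follow the randomisation or the sample-size assumption. Tested as two pooled means, it would be slightly conservative (about 4-5%) under shared counselor effects, or modestly anticonservative (about 5-9%) if counselors differ in delivering CBI. Both ranges assume an ICC of 0.01 to 0.10, 20 counselors and about 7.5 clients per arm per counselor. The second also treats counselors as a sample from a wider population. Since the protocol gives no ICC, the direction cannot be determined. Confidence is high in the mismatch and low in any particular error rate.

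**What to change.** - **Item 5:** replace the pooled change contrast with a comparison of follow-up scores adjusted for the baseline score, with counselor included as the randomisation stratum.
- **Item 14:** state what the 1.5 represents, namely the unit, the ICC and the cluster size.
- **Sensitivity analysis:** let the CBI effect vary by counselor, with small-sample degrees of freedom, or use a one-sample t-test on the within-counselor differences.

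The cost is wording. Baseline scores are collected, and the investigators' master lists are kept per counselor, so the identifier exists. Counselor as a fixed stratum uses 19 degrees of freedom against about 225 expected completers (300 × 0.75). The sensitivity analysis loses a little power if counselors do not differ, about 92-93% against 96% at d = 0.5. No visit, procedure or participant burden changes.
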